### Design

The study has been designed as a multi-centre, open, randomized controlled trial. Participating centres should have adequate experience with the treatment of patients with spinal cord trauma and neurosurgical facilities should be available on a 24 hours-a-day basis. All primary analyses will be performed on an intention-to-treat basis comparing the two strategies.

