### Sample size

Power calculations are hampered by the scarcity of data on clinical outcome in this patient group. The minimal clinically important difference in mJOA has been estimated in an earlier trial [9,13]. A difference of at least two points on the modified JOA functional score is considered significant. The difference is expected to be mainly allocated to the function of the arms and legs. Based on literature, a standard deviation of 2 is assumed. This estimate was confirmed by asking three experienced cervical spine surgeons (members of the board of the CSRS-es).

The sample size is calculated as follows: a two group student test with a 0.05 two sided significance level and a power of 95 % will need a sample size per group of 27 to detect a significant difference. Considering a ten percent loss in follow up a total of 30 individuals per group need to be included.

During the conservative treatment some patients will require surgical decompression due to for example neurological deterioration. It is estimated that it will occur in 20% of the patients. Although this is not considered a failure of treatment, the sample is increased to 36 patients per group in order to maintain the same power.

Only patients allocated to the conservative group who are offered surgery within 24 hours post-trauma, are considered crossovers. This number is expected to be very low. However, after completion of the trial this will be evaluated and a separate per-protocol analysis performed if significant cross over occurred.

Five centres in the Netherlands will participate and is estimated that its conclusion will be within 2 years.

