### Statistical analysis

Baseline characteristics are reported using descriptive statistics. Any imbalance characteristics found visually will be account for in analysis of primary outcome.

Since the primary outcome of the two strategies is compared after two years, a test for independent samples will be used (student-t test). To see if differences at all time points are present, these are assessed by computing both the main effect of the treatment and the interaction between treatment and time in a mixed linear model.

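### The primary two-year t-test leaves admission and interim mJOA unused and cannot carry the adjustment the plan promises; the 24-month contrast from the planned mixed model should be primary

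*Protocol article*

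**What the plan says.** The Outcomes section names mJOA at two years as the primary outcome. The Statistical analysis section compares the two strategies on it with a Student t-test for independent samples. The same section says that baseline imbalances noticed on inspection will be taken into account when the primary outcome is analysed. For differences at the separate time points, it says that "these are assessed by computing both the main effect of the treatment and the interaction between treatment and time in a mixed linear model".

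The Design section states: "All primary analyses will be performed on an intention-to-treat basis comparing the two strategies". The Sample size section raises 27 per group to 30 for attrition ("Considering a ten percent loss in follow up a total of 30 individuals per group need to be included"). It then allows for later surgery in the conservative arm: "the sample is increased to 36 patients per group in order to maintain the same power". Table 1 schedules mJOA at admission, 6 weeks, 12 weeks, 12 months and 24 months.

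**The concern.** Three choices in the Statistical analysis section fit together badly.

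- **The named test cannot do what is asked of it.** A two-sample t-test takes no covariates, yet the section promises adjustment. What is adjusted for is to be decided after looking at the baseline table, so the primary model is not fixed in advance.
- **The named test uses only the last of five mJOA assessments.** Admission mJOA is likely to predict the 24-month score, and the interim scores carry information on patients whose 24-month score is missing. The plan expects about 10% loss and already includes a mixed model that could use these data.
- **The main effect does not answer the question put to the mixed model.** The question is whether the arms differ at each time point. A main effect averages over visits, and the interaction tests whether the difference changes. Neither is a difference at a given visit.

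At stake are a wider confidence interval than the data require, an estimate exposed to loss that depends on earlier scores differently in the two arms, and a secondary result that is easily misread.

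**Working it through.** **1. The plan's own figures.** Inputs, all from the Sample size section: the test ("a two group student test with a 0.05 two sided significance level"), the power and number ("a power of 95 % will need a sample size per group of 27 to detect a significant difference"), the difference of 2 points ("A difference of at least two points on the modified JOA functional score is considered significant") and the SD ("Based on literature, a standard deviation of 2 is assumed").

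- Normal approximation: n = 2(1.960 + 1.645)² × 2² / 2² = 25.99, so 26 per group.
- Noncentral t: power 0.9424 at 26 and 0.9501 at 27. The stated 27 is exact.
- Attrition: 27 / 0.9 = 30. Allowance for later surgery: 30 × 1.2 = 36.
- With 36 recruited and 10% lost, 36 × 0.9 = 32.4. At 32 per group, t-test power for 2 points is 0.976.

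The t-test on observed scores is therefore not underpowered under the stated inputs.

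**2. Precision given up.** The documents give no correlation between visits, so a range is assumed.

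- t-test after 10% loss: SE = 2 × √(2/32.4) = 0.497.
- Admission score as covariate, complete data: SE = 2 × √(1 − ρ²) × √(2/36), which is 0.408, 0.337 and 0.283 for ρ = 0.5, 0.7 and 0.8.
- Equivalently, the 25.99 per group is multiplied by 1 − ρ². That gives 24, 20 and 14 per group for ρ = 0.3, 0.5 and 0.7.

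**3. Simulation with loss after 12 months.** Settings: 36 per group, SD 2, true differences 0, 0.5, 1, 1.5 and 2 over the five visits, equal correlation ρ between visits, 2,000 replicates. The Monte Carlo error of a mean is about 0.5/√2000 = 0.011.

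- (a) Loss unrelated to outcome.
- (b) Loss depends on the 12-month score in the same way in both arms.
- (c) Loss depends on it in opposite directions by arm (log-odds +1 and −1 per SD).

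"RM" is the estimate that uses admission and interim scores.

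| ρ | (a) SE, t-test / RM | (b) mean, t-test / RM | (c) mean, t-test / RM | (c) at the 20% loss setting, t-test / RM |
|---|---|---|---|---|
| 0.5 | 0.488 / 0.423 | 2.019 / 2.014 | 2.244 / 2.009 | 2.409 / 2.000 |
| 0.7 | 0.502 / 0.355 | 2.008 / 2.010 | 2.320 / 1.988 | 2.578 / 2.013 |
| 0.8 | 0.499 / 0.290 | 2.000 / 2.005 | 2.385 / 1.993 | 2.657 / 2.000 |

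Columns (a) to (c) use the 10% loss setting. In (c) the t-test is off by 0.24 to 0.39 points, or 12% to 19% of the 2-point target. The sign would reverse if the directions were swapped between arms.

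Limits: RM was a regression form equivalent to likelihood estimation when only the last visit is missing, not a fitted mixed model. Its power was not simulated. Realised loss in (c) was about 13% at the 10% setting.

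**4. The averaged main effect.** The trajectories are assumed.

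| Difference at the four follow-up visits | Average, follow-up only | Average with admission as a response (0) |
|---|---|---|
| 0.5, 1, 1.5, 2 | 5/4 = 1.25 | 5/5 = 1.0 |
| 2, 2, 2, 2 | 8/4 = 2.0 | 8/5 = 1.6 |

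In both rows the 24-month difference is 2. The average matches it only when the effect is constant and admission is left out.

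**The case against.** The t-test matches the endpoint, its time point and the sample size method, and its power is ample. The interaction term gives the planned mixed model the structure from which visit contrasts can be drawn; the article merely does not name them. Missing-data handling is commonly left to a full protocol or SAP, and neither is shown. All of this stands, and it limits the point to an improvement in the choice of analysis.

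Several stronger readings are tempting and should be resisted.

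- **That the t-test contradicts intention-to-treat.** The Design section uses the term for comparing the two allocated strategies. Using observed outcomes by allocated arm does not breach that, and nothing in the article rules out imputation.
- **That the t-test is valid only if loss is unrelated to earlier recovery.** Scenario (b) shows no visible bias when the relation is the same in both arms. Nothing in the documents indicates the opposing pattern in (c); it shows what could happen, not what is expected.
- **That the bias has a known size.** For example, 5% loss in one arm and 15% in the other, with lost patients 3 points worse, gives 0.15 × 3 − 0.05 × 3 = 0.30 points. All three inputs are assumed, and a mixed model would remove only the part that earlier scores explain.
- **That the main effect will be diluted by admission.** The article does not say that admission is a response in the model.

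The objection does not remove the mismatch between a covariate-free test and a promise to adjust on visual inspection, or the neglect of scores that the trial collects anyway.

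**Conclusion.** The concern holds as a matter of analysis choice. The primary comparison is specified as a test that cannot carry out the promised adjustment, and the adjustment rule depends on the data. The test also leaves out four scheduled mJOA assessments that the planned mixed model could use.

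Using them lowers the standard error from 0.49–0.50 to between 0.42 (ρ = 0.5) and 0.29 (ρ = 0.8). It also keeps the estimate within about 0.01 of the truth where opposing loss by arm moves the t-test by 0.24 to 0.39 points. These sizes rest on assumed correlations, a normal outcome with the plan's SD of 2, and loss that the 12-month score explains. The precision gain needs no loss mechanism, only a correlation between earlier and 24-month scores.

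The mixed-model criticism survives in part: the model is suitable, but an averaged main effect is the wrong quantity to report for differences at each visit.

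**What to change.** In the Statistical analysis section:

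- Make the primary analysis the 24-month treatment contrast from the mixed model already planned. Responses are mJOA at 6 weeks, 12 weeks, 12 months and 24 months. Fixed effects are treatment, visit as a category and treatment-by-visit.
- Enter admission mJOA as a prespecified covariate, not as a response. This replaces adjustment for imbalance found by inspection.
- Report the treatment difference with its confidence interval at each visit, in place of the averaged main effect.
- Keep the two-year t-test as a supportive analysis.
- Add a separate sensitivity analysis for deaths, because the model would treat scores after death as missing at random.

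The cost is a change of wording and slightly more analysis work. No extra patients or measurements are needed, and the stated 36 per group need not change. The primary result would rely on data being missing at random given the admission and earlier follow-up scores, and the plan should say so.

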## Discussion

Although already described in 1887 [14], traumatic central cord lesion has first been defined by Schneider in 1954 [15]. It was characterized by disproportionately more motor deficit of the arms and especially the hands than the legs, bladder dysfunction and varying degrees of sensory loss below the lesion. It was most frequently seen in hyperextension injuries causing squeezing or pinching of the spinal cord both anteriorly and posteriorly. Since its definition it was considered as a separate entity. Recently, it was shown that it is just a form of incomplete spinal cord lesion [1] therefore we abandoned the use of the term traumatic central cord syndrome.

Since the description of traumatic central cord syndrome its treatment has been the subject of discussion. In 1954 surgical decompression was even contraindicated because spontaneous improvement or complete recovery may occur [15]. At this moment either surgical decompression or conservative treatment are favoured. If a surgical decompression is chosen, the timing of the procedure is also debated.

From a biological standpoint early decompression seemed to be the most effective due to the prevention of secondary damage [16]. In this study early surgery is defined as decompression within 24 hours. Due to referral patterns it was thought that a more strict time schedule would negatively interfere with the inclusion of the patients. The operative approach to decompress will be dependent on the surgeon. It is thought that the approach does not contribute to the clinical effect as long as the spinal cord is decompressed effectively.

In this study, surgical decompression is solely compared to a standardized conservative treatment. The conservative treatment offered in both treatment arms will be equal.

As primary endpoint the score at the translated mJOA was chosen. Although it was developed for evaluation of symptomatic cervical myelopathy due to degenerative changes, its simplicity and the evaluation of the functional impairment by the mJOA justified the choice above the others. The scale is completed with the help of the patient or even by the patient self. The mJOA addresses the function of the upper limbs, lower limbs and urinary sphincter. In fact, the signs and symptoms of cervical spondylotic myelopathy resemble those of an incomplete spinal cord lesion. Furthermore, functional outcome is the most important for the patient treated for a spinal cord lesion as it will directly influence his/her quality of life.

The ASIA score has been designed for the evaluation of traumatic spinal cord lesion, however it was not a functional score. On the other hand, SCIM III has recently been developed to evaluate the functional impairment [10]. However, the experience with the scale is limited and a clinically minimal important difference has not been established. It will be measured at each visit and its value in comparison to the other scales, including the scales for quality of life, will be established.

Since the function of the hand is generally more affected than the function of the lower limbs in ICSCL, extra attention is given to a more specific test for studying the function of the hand. For this purpose, a questionnaire to be self assessed was chosen, DASH. Apart from the self assessment the validation of the translation into Dutch is an advantage.

The major goal of the study will be to compare clinical outcome measured by functional scales and quality of life scales between two established treatment options. Parallel to this objective, direct and indirect costs will be evaluated from a societal perspective. Analysis of clinical outcome in relation to costs is part of the study.

Several problems may arise. The recruitment of patients may be hampered by the emotional distress during the time that the patient must be included. In addition to an informed consent form a legal representative is also required, but this does not preclude a delay in the inclusion since the legal representative may be in emotional distress as well. Furthermore, MRI may disclose findings like hemorrhage within ligaments or discs or other abnormalities suggesting instability. Even if instability is not shown on the standard radiographs, surgeons might be willing to offer the patient surgery. Although a patient could have been included in the trial, surgeons’ preference prohibited inclusion. Participating surgeons are encouraged to follow the protocol. In case of doubt, the project leader is always willing to deliberate the case including the findings at radiographs. However, it cannot be prevented that potential candidates are sometimes not included due to a surgeon’s preference. The freedom to choose for a surgical approach including the use of implants may interfere with the results. However, since every patient is unique a standard approach cannot be given. Therefore, a more pragmatic approach is chosen requiring adequate decompression of the spinal cord.
